## Treatment administration

### 6.2.1 Amount, dose, concentration, frequency

Subjects will receive equivalent of 3 servings of coffee (one of the three study treatment conditions) immediately after baseline testing is completed. Subjects will consume the coffee orally within 15 minutes. In total, each subject will complete three treatment conditions: CGA (540mg CGA mixed in 5460mg placebo matrix;) instant decaffeinated coffee (6 grams); and placebo (6 grams maltodextrin and CHE mixed with coffee flavour and colour). The coffee beverage will be prepared by the investigator at the study site. Milk and sacchran can be added by participants to suit their own taste. Note that in a previous pharmacokinetic study conducted at Nestlé, no modulations to the bioavailability of Nescafé PROTECT was found when black coffee was mixed with milk (Renouf et al., 2008).

### Route of administration

Oral administration.

### Subject compliance

The product will be consumed under supervision of the investigator/research assistant. Subjects will receive a comprehensive list of foods that must be avoided 24 hours prior to each training and testing session (Appendix 2). Participants will receive a reminder phone call prior to each training and testing day to increase compliance.

## 6.3 Concomitant diet and treatment

Any medication/treatment initiated during the course of the trial must be recorded in the case report form.

### 6.3.1 Permitted concomitant diets/treatments/medications

Medication for the control of cholesterol and blood pressure is accepted. A standard breakfast/lunch will be provided to all subjects.

### 6.3.2 Unauthorized concomitant diets/treatments/medications

No coffee is permitted for 24 hours prior to each training and testing session. In addition, participants must abstain from caffeine-containing foods and beverages, alcohol, no foods containing chlorogenic acids, and only food with low polyphenol content for 24 hours prior to each training and testing session. A list of foods to be avoided will be provided to all participants (Appendix 2). The use of any psychoactive medications is prohibited throughout the study.

## Product handling

### 6.4.1 Storage and distribution

All study products will be supplied by Nestlé without charge to the investigator. The study products will be supplied to the study site after the investigator has obtained approval from the Ethics Committee and applicable regulatory authorities.

The study product will be stored according to specific instructions accompanying the shipment. Dispensing shall be done on a day-to-day basis by the investigator

### Product accountability and reconciliation

All test articles (investigational product and control) received and dispensed by the investigator will be inventoried and accounted for throughout the trial period by the investigator on the corresponding “product distribution list” (to be delivered during the trial launching visit).

The investigator agrees not to supply the test articles to any person except the subjects participating in this trial. Unused product must not be traded. Unused product remaining at completion of the study will be returned via the Nestlé representative or the sponsor can arrange with the investigator for it to be destroyed onsite with a proper certification of destruction.

# Definition of measures

Cognitive testing will consist of selected tests of attention, working memory, emotional attention, information processing speed, and reaction time performance.

## 7.1 Primary outcome measure

Rapid Visual Information Processing (RVIP) task is a test of sustained attention. This task also loads heavily on working memory. Single digits (1-9) are presented continuously in the middle of a computer screen in a semi-random order. Participants are required to press the response button as soon as they detect three consecutive odd or three even digits in ascending order (i.e. 2,4,6; 3,5,7; 4,6,8; 5,7,9). The digits are presented at a rate of 100 digits per minute. Stimulus duration is 600ms with no inter-stimulus interval. There are eight target sequences (i.e. potential correct hits) presented per minute (96 targets in total). The total duration of the task is 12 minutes. The outcome measure is the number of correct hits (accuracy).

## 7.2 Secondary outcomes measures: other cognitive tasks

- - Rapid Visual Information Processing (RVIP) as above. The outcome measure is the mean reaction time for correct hits and false alarm rate.
  - Inspection Time (IT) is a measure of perceptual speed. This task assesses the presentation time that a subject requires to discriminate between two possible stimuli. The task consists of a stimulus with two vertical parallel lines joined at the top by a horizontal line. There are two versions of the stimulus; either the left line is shorter than the right or the right line is shorter than the left. Stimuli are flashed on a computer screen and the participant is instructed to press a key corresponding to the side of the symbol that is shorter. Each stimulus presentation is followed by the presentation of a backward visual mask. This prevents further processing of the stimulus in iconic memory. The speed of stimulus presentation is varied according to the accuracy of the participants’ responses. The length of presentation of the backward visual mask also varies to determine the optimal visual encoding time. The objective is to respond as accurately, rather than as quickly, as possible. The duration of stimulus presentation is varied until an 80% accuracy level is obtained by the participant. This is taken as the outcome measure for speed of visual information processing speed.
  - Extended Serial Sevensis a computerised task measuring concentration and working memory. A random starting number between 800 and 999 will be presented on the computer screen. Participants are required to count backwards in sevens from the given number, as quickly and as accurately as possible. Responses are made using a numeric keyboard. The outcome measures are the total number of subtractions and number of errors. The duration of the task is 2 minutes.
  - Serial Threes is identical to Serial Sevens (see above), except that it requires serial subtractions of threes. The duration of the task is 2 minutes.
  - Emotional Face Recognition task is a measure of emotional processing and attention. This task requires participants to view pictures of facial affect consisting of three basic emotions (happy, sad and neutral) taken from the Ekman Pictures of Affect Series (Ekman and Friesen, 1976). To increase the difficulty of the task, for each actor, happy and sad faces are morphed with their neutral face (50% linear morph) as described previously. For each trial, a picture of a face depicting an emotional or neutral expression will be presented in the middle of the screen. Three emotion labels (happy, neutral, sad) will be presented simultaneously beneath the picture as a reminder to the participant of which response button corresponded to which emotion. The face stimuli will be 12 x 8 cm, and the emotion labels will be presented in a 3.4 x 2 cm text box. Participants will be seated 60 cm from the screen. The facial stimuli will be made up of six actors (3 males and 3 females), with each emotion presented 108 times (18 times by each actor), giving a total of 324 stimuli presentations. Each trial began with a fixation cross in the centre of the screen for about 300 ms, followed by the face (and the emotion labels) for 1200 ms. Participants are required to identify the faces as happy, sad or neutral by pressing a corresponding button on a button box. Participants are instructed to respond as accurately as possible. Immediately before the actual task, participants will perform a practice task consisting of photographs of the two unused actors from the Ekman series. Behavioural outcome measures are percent correct recognition (accuracy).
  - N-back task is a measure of sustained and selective attention and impulsivity. Single digits are presented on the screen. Participants are required to press ‘YES’ or ‘NO’ using a button box, to indicate whether the digit is the same as the *n* previously (e.g. 1-back the previous digit, 3-back the digit 3 previously). The task is scored for speed and accuracy. The duration of the task is approximately 4 minutes.
  - Reaction Time will be assessed with the Jensen box. This is an apparatus that distinguishes decision time and movement time from total reaction time. This apparatus has eight lights which are arranged in a semi-circular configuration. A response button is located adjacent to each light. A "home" button is situated in the centre of the panel. Subjects are required to press the home button until they see a target light and then to release the home button as quickly as possible and to press the response button adjacent to the stimulus light. Decision time (DT) is defined as the time from stimulus onset to the release of the home button, and movement time (MT) as the time from release of the home button to the depression of the stimulus button. Choice is manipulated by varying the number of stimulus alternatives, from 0 (i.e. one light at one possible location) to multiple (i.e. the stimulus may appear in any one of the eight light positions). Participants will be given several practice trials in the eight stimulus (i.e. eight lights) condition so that they can familiarise themselves with the task. DTs of less than 150 ms are discarded as outliers, as it has been argued that physiological limits prevent shorter DTs (Jensen, 1987). DTs over 999 ms will also be discarded and replaced with an additional trial. In addition, all DTs exceeding three SDs above the subject's mean DT are also discarded (Jensen, 1987). The outcome measures are the median, mean and intra-individual variability (*i - average standard deviation) of both DT and MT for all choice, intercept of the DT function across choice and the slope of this function.

## 7.3 Secondary outcome measures: Mood scales

Bond and Lader Visual Analogue Scales (VAS) (Bond & Lader, 1974) is a frequently used self-evaluation mood rating scale (Appendix 3). In total, 16 dimensions of mood are given. The participant is required to mark, on a 100 mm line to what extent the described state is appropriate to him/her at that moment in time. The Bond and Lader VAS discriminates three affective dimensions: alertness, contentment, and calmness.

Caffeine Research Visual Analogue Scales(Appendix 3) consists of seven visual analogue scales ("relaxed", "alert", "jittery", "tired", "tense", "headache", overall mood") that have previously been used in research into the effects of caffeine (Rogers et al., 2003). In addition, a single "mentally fatigued" visual analogue scale was included, as previous research has shown it to be sensitive to a caffeine-glucose drink (Kennedy & Scholey, 2004).

## 7.4 Other measures

- - Doppler Ultrasound measures blood flow both going towards the brain (in the common carotoid artery and internal carotoid artery) and in the brain (in the middle cerbral artery). The outcome varible is mean velocity.
  - Mini-Mental State Examination (MMSE) (Folstein et al., 1975) is a brief 30-point test that is commonly used to screen for dementia. The MMSE evaluates six areas of cognitive function: orientation, attention, immediate recall, short-term recall, language, and the ability to follow simple verbal and written commands. The MMSE is divided into two sections. The first part requires vocal responses to the examiner's questions. The participant is asked to repeat a short phrase after the examiner; to count backward from 100 by 7s; to name the current season and similar brief items. It tests the participants' orientation, memory, and attention. The maximum score for this section is 21. In the second part of the examination, the participant is asked to follow verbal and written instructions, write a sentence spontaneously, and copy a geometric figure. The test is not timed but usually takes less than 10 minutes to complete. Participants will be excluded if they score less than 24 on the MMSE. In an elderly population, a cut-off of 24 provides high sensitivity and specificity (Spreen & Stauss, 1991).
  - Blood samples will be obtained for internal analyses of the bioavailability of various polyphenols such as caffeic acid, ferulic acid, etc. Blood samples will be taken at baseline (during the training session), 10 minutes, 90 minutes, and 160 min post treatment consumption.

# Conduct of the trial

## 8.1 Study plan, flow chart

A flow chart of the testing schedule is outlined in Appendix 4.

A short telephone interview will be conducted will all potential subjects to ensure study criteria are met (i.e. see Section 5 Study Population). Successful volunteers will then attend one training session. Note that prior to the training session subjects will be a given a list of foods that need to be avoided prior to the training session. Specifically, subjects will be asked to abstain from caffeine-containing foods and beverages, alcohol, no foods containing chlorogenic acids, and only food with low polyphenol content for 24 hours prior to each testing session. During the training session, subjects will complete demographics and medical questionnaire, the MMSE, and informed consent will be obtained (if criteria are met). Subsequently, subjects will complete the battery of cognitive tests to familiarize subjects with study procedures and minimize procedural learning effects. A baseline blood sample will be obtained.

Approximately 24 hours prior to each testing session, subjects will receive a reminder telephone call that they must abstain from caffeine-containing foods and beverages, alcohol, no foods containing chlorogenic acids, and only food with low polyphenol content for 24 hours prior to each testing session. Subjects are instructed to arrive at the laboratory well rested (following a normal night’s sleep). At the beginning of each experimental session, bread with various spreads and orange juice will be provided. After the participant finishes eating, subjects will complete the mood visual analogue scales followed by the cognitive tests. The mood scales will be completed a second time immediately after baseline cognitive testing is finished. The battery of tests should take approximately 40 minutes to complete. Subsequently, baseline brain doppler blood flow will be obtained. Subjects will then be administered the equivalent of 3 servings of coffee, which must be consumed within 15 minutes.

Based on a previous pharmacokinetic study conducted at Nestlé, following oral ingestion of Nescafé PROTECT coffee, several polyphenol metabolites were shown to peak in plasma within 2 hours after coffee ingestion (Renouf et al., 2008). Based on these results and the results from the acute clinical decaffeinated coffee trial (08.17.NRC), cognitive testing will begin 40 minutes after treatment consumption.

Ten minutes following treatment consumption the first blood sample will be obtained. Forty minutes following treatment consumption participants will complete the mood visual analogue scales, followed by the cognitive tests, and again the mood visual analogue scales. A second blood sample will be obtained and brain doppler blood flow will be measured (approximately 90 minutes post treatment consumption). Participants will then rest for approximately 15 minutes before the final battery of cognitive and mood tests are administered 120 minutes post treatment consumption. Specifically, 120 minutes following treatment consumption, participants will complete the mood scales, followed by the cognitive test battery, and again the mood scales. A final blood sample will be obtained 160 minutes post treatment consumption.

Participants will complete the experimental session three times. Each experimental session will take approximately 4 hours to complete. Experimental sessions will be separated by at least a one-week washout period.

The time schedule for each experimental session will be as follows:

NOTE: baseline blood measures will be taken during training session. Subjects must adhere to restricted diet prior to training session also (see above)

- 0 - 15 min Breakfast/Lunch served

- 15 - 17 min Mood visual analogue scales

- 17 - 57 min Cognitive testing

- 57 - 60 min Mood visual analogue scales

- 60 - 70 min Brain blood doppler flow

- 70 - 85 min COFFEE CONSUMPTION

- 95 - 105 min Blood sample

- 125 - 127 min Mood visual analogue scales

- 128 - 173 min Cognitive testing

- 173 - 175 min Mood visual analogue scales

- 175 - 190 min Brain doppler blood flow and blood sample

- 205 - 207 min Mood visual analogue scales

- 207 - 250 min Cognitive testing

- 250 – 252 min Mood visual analogue scales

- 252 - 265 min Blood sample

- 265 min Finish

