### Form and dosage

All products will be in powder form.

Instructions for correct preparation will be printed on the label in English.

All coffee treatments will be dissolved and administered as a normal hot coffee drink. Prior to administration, one coffee sachet (6g) will be dissolved in 300 ml boiled water. Milk and sacchran can be added by participants to suit their own taste.

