**Food and drink to be avoided during 24 hours**

**prior to every testing session.**

| **Drinks**  **AVOID:** | **Drinks that are OK** |
| --- | --- |
| **All** types of tea (e.g. earl grey, green, black, Oolong)  Drinks containing tea (ready to be consumed, instant)  Herb teas  Coffee  Hot chocolate/Cacao/Nesquik/Milo | Hot milk |
| Fruit juice, in particular:  Orange juice  Grape juice  Apple juice | Cordial, lemonade, lemon drink, water |
| All alcohol |  |
| **Fruits, vegetables, nuts**  **AVOID:** | **Foods that are OK** |
| Blackberries | Banana |
| Green and red grapes | Melon |
| Raspberries | Pineapple |
| Strawberries | Pear |
| Blueberries | Carrot |
| Cherries | Pasta |
| **All** citrus fruit such as oranges, grapefruit, lemon, lime, tangerines | Rice |
| Plums |  |
| Apples |  |
| Raisons, Currants |  |
| Olives |  |
| Spinach |  |
| Asparagus |  |
| **All** Nuts, e.g. hazelnuts, walnuts, almonds, peanuts, etc |  |
| **Cereals and Breads**  **AVOID:** | **Foods that are OK** |
| Buckwheat | Cereals containing rice |
| Oats | White bread |
| Barley |
| Corn/Wheat |
| Broad beans |
| Lentils |  |
| **Desserts, sweets, biscuits**  **AVOID:** | **Foods that are OK** |
| Anything containing chocolate e.g. chocolate bars, chocolate, cakes, chocolate biscuits, chocolate cream, chocolate mousse, chocolate ice-cream | Plain yogurt |
| Cereal bars | Honey |
| Jams and frozen fruits |  |
| Nutella |  |
| **Other**  **AVOID:** | **Foods that are OK** |
| Olive oil | Vegetable oil |
| Grape oil |  |

Appendix No 3

MOOD VISUAL ANALOGUE SCALES

Appendix No 4

FLOW CHART

**V0**

**V1**

**V2**

1 week

1 week

1 week

**V3**

Wash-out

Wash-out

Wash-out

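### Each session starts with orange juice, an item the protocol's own low-polyphenol list tells subjects to avoid, 55 to 70 minutes before dosing; spreads, milk and sweetener are not fixed or recorded.

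*Protocol*

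**What the plan says.** **Run-in diet.** Section 6.3.2 bars caffeine, alcohol and foods containing chlorogenic acid, and allows "only food with low polyphenol content for 24 hours prior to each training and testing session". Section 5.2 repeats the rule as an inclusion criterion. Section 6.2.3 backs it with a food list and reminder calls.

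**Avoid list.** Appendix 2 applies to the 24 hours "prior to every testing session". Under drinks to avoid it has "Fruit juice, in particular", followed by orange, grape and apple juice. Under fruit it lists all "citrus fruit such as oranges, grapefruit, lemon, lime, tangerines". Under sweets it lists "Jams and frozen fruits" and Nutella. Honey and white bread are in the permitted columns, as are several drinks.

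**Session meal.** Section 8.1 says: "At the beginning of each experimental session, bread with various spreads and orange juice will be provided". Its timetable gives "0 - 15 min Breakfast/Lunch served". Section 6.3.1 calls the meal standard, and says it may be breakfast or lunch.

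**Test drink.** Section 6.1.2 says: "Milk and sacchran can be added by participants to suit their own taste". Section 6.2.1 repeats this. For milk it cites an earlier pharmacokinetic study of a named coffee product, which found no change in bioavailability.

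**Blood.** Sections 7.4 and 8.7 place the baseline sample at the training visit (V0) and three samples after treatment at each of V1 to V3. They are for plasma polyphenols and, in Section 8.7, glucose.

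**The concern.** The protocol goes to some length to have subjects arrive low in dietary polyphenols: an inclusion criterion, a food list and reminder calls. The site then serves an item from that list in the last 70 minutes before a polyphenol test product is drunk. Barring orange juice the day before and pouring it an hour before dosing cannot both serve the same purpose.

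What is at stake is mainly the blood data. Samples meant to show what the CGA drink and the decaffeinated coffee contribute to plasma polyphenols would also carry whatever the meal contributes. Glucose has the same problem after bread, spreads and juice. With no sample between meal and dose, the two sources cannot be separated within a visit.

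There is a second, smaller stake. If the spreads, the milk, the saccharin or the type of meal differ between a subject's three visits, they add within-subject variation to the comparisons that the crossover is meant to sharpen.

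**Working it through.** There is no plan figure to reproduce. The check compares the texts and uses the Section 8.1 timetable.

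**1. Meal against list**

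| Item in the session | Status in Appendix 2 |
|---|---|
| Orange juice | Named under avoid; oranges are also covered by the citrus entry |
| Spreads, not named | Undetermined: jams and Nutella are under avoid, honey is permitted |
| Bread, type not named | Undetermined: white bread is permitted, corn/wheat is under avoid |

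Only the juice is a certain mismatch.

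**2. Timing**

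Inputs: meal 0 to 15 min, drink 70 to 85 min, blood sampling from minutes 95, 175 and 252. The second sample shares the 175 to 190 slot with the Doppler, so 175 is its earliest time.

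- Start of meal to start of dosing: 70 − 0 = 70 min.
- End of meal to start of dosing: 70 − 15 = 55 min.
- End of meal to the three samples: 95 − 15 = 80 min, 175 − 15 = 160 min, 252 − 15 = 237 min.

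No blood sample falls between minute 15 and minute 70.

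**3. Consequence for blood**

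Write b for the V0 level, m(t) for the meal's contribution and c(t) for that of the test drink. If the subject arrives at a session at the V0 level, a sample reads b + m(t) + c(t). The rise from V0 is m(t) + c(t), so the meal is counted with the product. Taking the difference between two sessions of the same subject, CGA minus placebo, gives

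[m(t) + c_CGA(t)] − [m(t) + c_placebo(t)] = c_CGA(t) − c_placebo(t).

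The meal drops out, but only if m(t) is the same at both visits. The placebo session therefore controls for the meal to the extent that the meal is held constant. It shows meal plus placebo matrix, not the meal alone.

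**4. Consequence for RVIP accuracy**

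The same algebra applies. A common additive meal effect cancels from every treatment contrast. The cognitive baseline is also taken after the meal (17 to 57 min), and Section 9.5 adjusts for it. Bias would need an effect of the meal that differs by treatment. If instead the intake varies from visit to visit with variance v, independently of treatment and between visits, the variance of a within-subject difference rises by v + v = 2v before baseline adjustment. That is noise, and the documents give no value for v.

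**5. Drink additions**

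They are made in the test drink, so after randomisation. Sections 6.1.2 and 6.2.1 give no amount and do not ask that additions be recorded or repeated. The study cited in Section 6.2.1 concerns milk, bioavailability and another coffee product. It does not cover saccharin, or CGA in the maltodextrin and rice-cereal (CHE) matrix.

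**The case against.** **The list is not literally broken.** Its window is the 24 hours before a session, and the meal is inside the session. This stands. The conflict is with the purpose of the run-in, not with its letter. Nor does the juice touch the caffeine and alcohol rules or the one-week washout between treatments.

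**The meal is common to all three periods.** This also stands. With a post-meal cognitive baseline, an identical meal does not by itself bias the RVIP contrasts.

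**The blood samples are secondary and have a control.** Section 7.4 describes the polyphenol work as internal, and Section 9.2 lists no blood endpoint. Section 8.7 compares CGA with decaffeinated coffee, both after the meal, and the placebo session supplies a background curve. This limits the harm but relies on the meal being the same each time.

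**Stronger readings that the documents do not support:**

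- *That the spreads served are on the avoid list, or that subjects choose them freely.* No spread is named, honey is permitted, no text describes a free choice, and Section 6.3.1 calls the meal standard.
- *That milk was overlooked.* Section 6.2.1 gives cited support for it, though narrow.
- *That additions differ by treatment.* This is possible, because they are made to taste. But CGA and placebo share one flavoured and coloured matrix, and nothing shows that additions would differ.
- *That the meal costs a stated amount of power.* Shrinkage of the CGA effect would need the meal to interact with treatment. The documents give neither a polyphenol load for the meal nor any basis for such a figure.

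**Conclusion.** The point holds as a modest inconsistency. A juice named on the avoid list is served 55 to 70 minutes before dosing at every session, which defeats part of what the run-in is for. The measurable harm falls on the plasma polyphenol and glucose data. Every post-dose sample follows the meal, by about 80 to 237 minutes, and the only baseline precedes all session meals. The placebo session recovers some of this if the meal does not change between visits.

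For the primary outcome, no bias is shown and no size can be given. Spreads and drink additions that are neither fixed nor recorded could add within-subject noise of unknown amount.

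The conclusion rests on the timetable being followed as written and on the avoid list being meant to keep background polyphenols low at dosing. It is worth acting on because the remedy is cheap, not because the trial's main comparison is in danger.

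**What to change.** 1. Reconcile Sections 6.3.1 and 8.1 with Appendix 2, so that the standard session meal is spelled out and contains nothing from the avoid columns. The permitted columns already hold white bread, honey and several drinks.
2. Hold each subject's meal, including whether it is breakfast or lunch, and any milk or saccharin the same at V1, V2 and V3. Settle these before the first treatment visit.
3. Record the meal and the drink additions in the CRF at each visit.

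The cost is a different breakfast order, one CRF line and slightly less choice for subjects. No procedure, visit or sample is added.
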